#### 2.12.2 Distribution of pathogens on wound

Wound samples of participants were collected for pathogen isolation and cultured to perform identification on the automatic pathogenic microorganism identification instrument (Mark Biotechnology, United States). Weekly assessments were conducted during weeks 1–4 of intervention.

#### 2.12.3 Levels of inflammatory mediators

ELISA was used to measure the levels of IL-6 and TNF-α in related tissues of wound drainage collected from the participants. The streptavidin-peroxidase (S-P) method was used to perform immunohistochemical staining on wound edge tissue samples, which were observed under a 400-fold light microscope and semiquantitatively measured using a medical image analysis system. Weekly assessments were conducted during weeks 1–4 of intervention.

#### 2.12.4 Blood glucose

Blood glucose was measured four times per day by using a glucometer, including fasting and 2-h postprandial blood glucose of breakfast, lunch, and dinner.

### 2.14 Safety outcomes

The assessments were at T0 and T1.1. Heart rate, blood pressure, temperature, and respiration.2. Blood routine, stool routine, and urine routine.3. Liver function: alanine aminotransferase, aspartate aminotransferase, γ-glutamyl transferase, alkaline phosphatase, and total bilirubin.4. Renal function: blood urea nitrogen and creatinine.5. Electrocardiogram.

### 2.15 Adverse events

Every adverse event (AE) was recorded, including the start date, end date, degree, relationship between the study drug and AE, and whether the participant is still involved in the study. Any serious adverse event (SAE) was reported to the Research Ethics Committee (REC) within 24 h. If any AE happened on any participant, the researcher asked the participant to stop using the washing decoction and determine if the event is related to the study drug formulation. If necessary, researchers took emergency safety measures to protect the participant from direct harm. If AE persisted, we followed it up until it was resolved. The AE in this study does not include complications clearly related to anal fistula, such as necrosis, prolonged healing, discharge, infection, pain, and itching.

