The Jiedu Shengji decoction (JSD) is a widely used external washing decoction in clinical practice, which has the functions of removing toxins for detumescence, discharging pus, and promoting granulation. The main botanical herbs in JSD are Zi Cao (*Arnebia euchroma* (Royle) Johnst.), Dang Gui (*Angelica sinensis* (Oliv.) Diels.), Ru Xiang (*Boswellia carterii* Birdw.), Mo Yao (*Commiphora myrrha* (T.Nees) Engl.), Xue Jie (*Daemonorops draco* (Willd.) Blume), Bing Pian (*Cinnamomum camphora* (L.) J.Presl), Bai Zhi (*Angelica dahurica* (Hoffm.) Benth. Et] Hook. f. ex Franch. et Sav), and Er Cha (*Acacia catechu* (L. F.) Willd). Preliminary studies have found that JSD can significantly reduce wound edema after anal fistula surgery, reduce nerve sensitivity, ease the pain in patients, and promote wound healing. However, this study was limited by its single-center and non-double-blind design. Therefore, a multi-center, double-blind, randomized, controlled clinical trial is needed to further determine the efficacy and safety of JSD in the treatment of postoperative wounds in diabetic patients with anal fistula. We proposed that patients treated with JSD will have more positive clinical outcomes than those with placebos.

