Bai Zhi [*Angelica dahurica* (Hoffm.) Benth. Et] Hook. f. ex Franch. et Sav]	Roots	Sichuan Chinese Herb Preparation Co., Ltd., Sichuan, China	20	Washing and sitz bath for 30 min	Liquid, 200ml, once a day, last 4 weeks	Y-registered in relevant administration	Y-prepared according to the manufacturer	The drugs are sealed and stored in a Chinese medicine warehouse at 0–30°C and 45–75% humidity
Ercha [*Acacia catechu* (L. F.) Willd]	Dry extract of skin, branch, and stem	Sichuan Chinese Herb Preparation Co., Ltd., Sichuan, China	20	Washing and sitz bath for 30 min	Liquid, 200ml, once a day, last 4 weeks	Y-registered in relevant administration	Y-prepared according to the manufacturer	The drugs are sealed and stored in a Chinese medicine warehouse at 0–30°C and 45–75% humidity

The placebo group was given placebos made of excipients and flavoring agents. Placebo formula: pyrosyrup (edible), apple green (edible), and lactose (medicinal). Placebos were packaged, shaped, and colored to be the same as JSD. Placebos were produced by the Placebo Experimental Center of School of Pharmacy, Chengdu University of Traditional Chinese Medicine, which had no efficacy or side effects. The external washing decoction was placed in a special vessel and air-dried to lukewarm for patients to take sitz bath for 30 min/time. Then, the bases of incisions were packed outward along with a gauze in moderate tightness. The incisions were covered with sterile gauze and fixed with adhesive plaster. The wound dressing was changed once a day for 4 weeks. We followed up the participants at the 8th, 12^th^, and 16th weeks after the dressing change was finished to record and analyze the recurrence.

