### 2.12 Primary outcomes

#### 2.12.1 Wound healing

Assessments were at T0, T1, T2, T3, and T4. At the same time, weekly assessments were conducted during weeks 1–4 of intervention.1) Wound healing rate: The wound area on the first postoperative day was the original area. The maximum length and width of the wound were measured with the calculated area. Formula: Wound healing rate = (original area-current area)/original area × 100%.2) Wound healing time: From the start of the dressing change to the complete epithelialization and healing of the wound.3) Wound secretion score (Table 2) (Gould et al., 2021): Wound with abundant secretion, two or more pieces of penetrated gauze, dressing change more than twice a day, 3 points; wound with much secretion, one piece of penetrated gauze, dressing change twice a day, 2 points; wound with little secretion, no penetrated gauze, 1 point; and wound with smooth surface and no obvious secretion, 0 point.4) Wound edema score (Table 2) (Gould et al., 2021): Wound with severe edema which is significantly more than the wound edge, surgical resection needed, 3 points; wound with obvious edema which is more than the wound edge, need dressing change to remit, 2 points; wound with mild edema, 1 point; and wound with no edema, 0 point.5) Granulation tissue color score (Table 2) (Gould et al., 2021): Bright red, 1 point; light red, 2 points; and purple, 3 points.6) Anal function evaluation: The Wexner incontinence score was used to evaluate the anal function of participants after wound healing (Zhang et al., 2020a), including the ability of the anus to control the intestinal fluid, bowel gas, and loose and formed stools.7) Anal pain score: The pain index tested before the dressing change on the first postoperative day was the baseline pain. The pain index after the first postoperative day was tested within 2 h after the dressing change. Pain values were tested using the visual analogue scale (Anal pain visual analogue scale, VAS) (Bondi et al., 2017).

**TABLE 2 T2:** Scale for assessing wound healing.

Wound secretion score (Gould et al., 2021)	Score
Would with smooth surface and no obvious secretion	0
Would with little secretion and no penetrated gauze	1
Wound with much secretion, one piece of penetrated gauze, and dressing change twice a day	2
Wound with abundant secretion, two or more pieces of penetrated gauze, and dressing change more than twice a day	3
Wound edema score (Gould et al., 2021)	Score
Wound with no edema	0

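### The adverse event definition drops local wound complications attributed to the fistula; necrosis, itching and clinical infection are then recorded nowhere else, so local safety is incompletely captured.

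*Protocol article*

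**What the plan says.** The Introduction gives safety as an aim alongside efficacy: a multi-centre, double-blind randomised trial "is needed to further determine the efficacy and safety of JSD in the treatment of postoperative wounds in diabetic patients with anal fistula". Section 2.8 describes a topical product. The decoction is "air-dried to lukewarm for patients to take sitz bath for 30 min/time", and Table 1 gives once a day for 4 weeks.

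Section 2.14 lists the safety outcomes and opens "The assessments were at T0 and T1.1. Heart rate, blood pressure, temperature, and respiration" (the second 1 is the list number). The remaining items are routine blood, stool and urine tests, liver and renal function, and ECG.

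Section 2.15 requires every adverse event to be recorded with dates, degree and relationship to the study drug, and serious ones to be reported to the ethics committee within 24 hours. It closes with the exclusion: "The AE in this study does not include complications clearly related to anal fistula, such as necrosis, prolonged healing, discharge, infection, pain, and itching". It also ties an action to adverse event status: "If any AE happened on any participant, the researcher asked the participant to stop using the washing decoction and determine if the event is related".

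**The concern.** A wash held against an open wound for half an hour a day would be expected to do harm, if it does any, mainly at the wound. The exclusion names events of that kind. It settles their cause before anything is recorded, although the adverse event form already has a relationship field for that purpose.

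The protocol itself treats these complications as common in this population: the Introduction mentions infection and necrosis, and the Discussion mentions infection, pain, itching and exudation. The natural default is therefore to blame the fistula. An event set aside in this way would not be tabulated, would not receive a causality assessment, and has no stated route to the serious event report. Events that were never recorded cannot be recovered at analysis. The randomised placebo arm already accounts for the background rate, so a comparison between arms does not need the exclusion.

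**Working it through.** The plan gives no figure on this point, so there is none to reproduce. The main check sets the six excluded terms against the outcome sections.

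- Pain: measured. Section 2.12.1 says "Pain values were tested using the visual analogue scale".
- Discharge: measured by the wound secretion score, 0 to 3 (2.12.1, Table 2).
- Prolonged healing: measured by healing time and healing rate (2.12.1).
- Infection: measured in part. Section 2.12.2 has weekly culture in weeks 1 to 4, which identifies organisms but does not record clinical infection, its grade or its seriousness.
- Necrosis: no outcome in 2.12 to 2.14.
- Itching: no outcome in 2.12 to 2.14.

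Count: 3 measured, 1 in part, 2 not at all. The 2.12.1 outcomes are assessed weekly in weeks 1 to 4 and at T0 to T4. None of the items in 2.14 concerns the wound.

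The next step is an illustration of what non-recording does. Inputs: n = 30 per arm (2.16). The event rates and the share q of events attributed to the fistula are assumed, because the article gives neither.

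1. Chance of seeing at least one event in an arm when all are recorded, 1 − (1 − p)^30:
   - p = 1%: 1 − 0.99^30 = 0.26
   - p = 5%: 1 − 0.95^30 = 0.79
   - p = 10%: 1 − 0.90^30 = 0.96

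   For an event type that is always attributed to the fistula, the chance is 0 at any p.

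2. Expected recorded events with true rates of 10% and 30%, 30 × p × (1 − q), with the same q in both arms as blinding would encourage:
   - q = 0: 3.0 versus 9.0, difference 6.0
   - q = 0.5: 1.5 versus 4.5, difference 3.0
   - q = 0.8: 0.6 versus 1.8, difference 1.2
   - q = 1: 0 versus 0, difference 0

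   Equal attribution in the two arms still shrinks the difference in proportion to 1 − q.

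3. For scale, power to show 10% versus 30% with 30 per arm, two-sided 5%, is about 0.49 even with full recording. The trial is a weak detector of local harm to begin with.

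**The case against.** A reader might infer that all six event types vanish from the trial and that its safety question cannot be answered. The documents do not support that, for four reasons.

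- The exclusion is conditional. It covers only complications clearly related to the fistula; a local event judged doubtful, or due to the wash, remains an adverse event. The judgement is made blind (2.10), which limits differential attribution by arm.
- Pain, discharge and healing are compared between arms as primary outcomes. Oedema and granulation colour are also scored. An excess in those directions could show in the main results.
- Other adverse events and the systemic safety measures are still collected.
- The article condenses a fuller protocol, which may contain attribution criteria.

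Two further inferences also go too far. Section 2.15 gives no definition of a serious event, so the article does not establish that a serious wound infection would escape the 24-hour report; it leaves this unclear. Section 2.18 does not say which data the monitoring board receives, so it cannot be said that the board would miss these events.

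All of this narrows the point without removing it. Blinding does not restore events that were never recorded. Mean scores do not replace individual events with dates, grade, relatedness and outcome. The efficacy outcomes are also an imperfect backstop: under 2.7 a participant who stops study medication leaves the study, and under 2.15 any adverse event leads to a request to stop. Some participants with bad local reactions may therefore drop out of the wound outcomes too, although 2.7 does require withdrawals to be recorded and reported.

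**Conclusion.** The point holds in a limited form. Section 2.15 decides cause before recording for the local events most relevant to a wound wash. Two of the six named events have no other record and a third has only a partial one. Local safety is incompletely captured, and possibly selectively, because what is kept depends on an attribution for which the article gives no criteria.

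The numerical loss cannot be derived from the documents. It depends on the true event rates and on the share attributed to the fistula, both assumed above, and a complete loss requires every case to be so attributed. The conclusion rests only on the wording of 2.15 and the absence of these events from 2.12 to 2.14. Systemic safety, pain, discharge and healing are not affected in the same way.

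**What to change.** Add to section 2.15 a separate record of local wound events, covering at least necrosis, clinical wound infection and itching. Complete it in both arms regardless of presumed cause, with start and end dates, grade and outcome, and with relatedness judged blind and entered as its own field. Tabulate these events by arm, and state that serious ones are subject to the 24-hour report.

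Simply deleting the last sentence of 2.15 is not advisable. Ordinary postoperative pain or discharge would then count as an adverse event. As written, that would bring in the stop instruction in 2.15 and, through it, the removal rule in 2.7. The sponsor must reconcile both passages with the new record; no clinical rule is proposed here.

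The cost is protocol wording, ethics approval of the change under 3.2, extra form entries at dressing changes that already take place daily, and higher reported event counts. Recruitment began in June 2022 (3.1), so the report should give the date from which the record was kept, since earlier events may not have been captured on the same basis.

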### 2.16 Sample size

According to the sample size estimation method for the comparison of two sample means, we preset the sample size of the placebo group and the intervention group for them to be equal. The calculation formula is as follows:
$$n=2\sigma^{2}\times \frac{f\left(\alpha ,\beta \right)}{{\left(\mu_{1}-\mu_{2}\right)}^{2}},$$

where *n* represents the overall sample size of the study, μ1 and μ2 are the mean values of the control group and the test group, respectively, and σ is the standard deviation. We set that the probability of making type I error in this study shall not be greater than 5%, and the probability of making type II error at the same time shall not be greater than 10%, that is, α = 0.05 and β = 0.1. Referring to Chinese literature reports on TCM external washing for the treatment of postoperative wound of anal fistula, the wound healing rate (%) in literatures was set as the clinical efficacy observation, the mean value was 33.35, and the standard deviation was 2.29 in the intervention group, and the mean value was 27.33 and the standard deviation was 2.67 in the placebo group. The estimated loss of the follow-up rate was 20%, so the total study sample size was 60, of which 30 was for the intervention group and 30 was for the placebo group.

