### 2.11 Outcome measures

Assessments were performed at the baseline (T0), 4 weeks after the final treatment (T1, primary endpoint), 8 weeks after the final treatment (T2, secondary endpoint, first follow-up 8 weeks after the final treatment), 12 weeks after the final treatment (T3, tertiary endpoint, second follow-up 12 weeks after the final treatment), and 16 weeks after the final treatment (T4, final endpoint, third follow-up 16 weeks after the final treatment). The timeframe of data collection and assessments is shown in Figure 3 (the SPIRIT figure).

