### 2.20 Data analysis

All data analyses were conducted by SPSS 24.0 software. Student’s t-test was performed on continuous normally distributed variables, the Wilcoxon rank-sum test on non-normal variables, and Pearson’s χ^2^ test on categorical variables. Data were presented as the mean ± standard deviation for continuous variables or percentage values for categorical variables. The statistical significance level was set at *p* < 0.05, and all the statistical tests were two-sided.

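### The formula and inputs in section 2.16 give about 4 to 5 patients per group, not 30, and n is labelled as the overall size when the formula gives the size per group

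*Protocol article*

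**What the plan says.** Section 2.16 of the protocol article uses the formula for comparing two means in equal groups, n = 2σ²·f(α,β)/(μ1−μ2)², and says that n "represents the overall sample size of the study". The error rates are "α = 0.05 and β = 0.1". The outcome is the wound healing rate in per cent, with values taken from Chinese literature on external washing: "the mean value was 33.35, and the standard deviation was 2.29 in the intervention group". For placebo, the corresponding figures are 27.33 and 2.67. Loss to follow-up is put at 20%. The section then concludes "so the total study sample size was 60, of which 30 was for the intervention group and 30 was for the placebo group". It shows no intermediate value of n and gives no other reason for 60.

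Section 2.16 does not say whether the test is one- or two-sided. Section 2.20 settles this: "all the statistical tests were two-sided".

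**The concern.** Every input to the formula is printed, so the result can be checked directly. Two things look wrong. First, the expression with 2σ² in the numerator is the number needed in each of two equal groups, yet it is defined as the size of the whole trial. Secondly, a difference of 6.02 points against SDs near 2.5 is a very large standardised effect. Such an effect needs only a handful of patients, not 30 per arm.

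At stake is the only sample size justification in the document. The section moves from error rates, means, SDs and loss straight to 60. A reader will therefore take 60 to be the number that gives 90% power for a 6-point difference in healing rate. If 60 does not come from those inputs, the reader cannot tell what the trial was sized to detect.

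**Working it through.** **Inputs.** From section 2.16: means 33.35 and 27.33, SDs 2.29 and 2.67, α = 0.05, β = 0.1, equal groups, 20% loss. From section 2.20: two-sided tests.

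**Attempt to reproduce 60 with the plan's own formula**

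- Difference: 33.35 − 27.33 = 6.02; squared, 36.24.
- Pooled variance: (2.29² + 2.67²)/2 = 6.186, so SD = 2.487.
- f(α,β) = (1.960 + 1.282)² = 10.507.
- n = 2 × 6.186 × 10.507 / 36.24 = 3.59, rounded up to 4 **per group** (8 in total).
- With 20% loss: 4/0.8 = 5 per group, 10 in total.

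**Variants, n per group before loss**

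| SD used | Two-sided | One-sided |
|---|---|---|
| 2.487 (pooled) | 3.59 → 4 | 2.92 → 3 |
| 2.29 | 3.04 → 4 | 2.48 → 3 |
| 2.67 | 4.13 → 5 | 3.37 → 4 |

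After 20% loss, these range from 4 to 7 per group. If n is read as the overall size, as the text labels it, the total before loss is only 4 to 5 (two-sided), which is further still from 60. None of these variants comes near 30 per group.

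**Exact t-test.** The normal approximation is poor at such small sizes. With the pooled SD, two-sided at 5%:

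- 4 per group gives 81.2% power.
- 5 per group gives 91.6% power.

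The exact requirement is therefore 5 per group. With 20% loss, 5/0.8 = 6.25, so 7 per group, 14 in total.

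**What 60 delivers.** After 20% loss, 30 × 0.8 = 24 evaluable per arm. Two-sided 5% t-test:

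- On the stated inputs, the standardised effect is 6.02/2.487 = 2.42 and power exceeds 99.9%.
- 90% power is reached at a difference of 0.956 SD, and 80% at 0.826 SD.
- For 24 per arm to mean 90% power for 6.02 points, the SD would have to be 6.02/0.956 = 6.3, about 2.5 times the stated value (6.3/2.487).

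**Illustration under assumed SDs** (not given in the document): power for 6.02 points with 24 per arm is 72% if the SD is 8 points and 53% if it is 10 points.

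**The case against.** The strongest reply is that the slip does no harm. The protocol requires that "the probability of making type II error at the same time shall not be greater than 10" per cent. On its own means and SDs, 24 evaluable patients per arm meet that requirement with a wide margin. The error runs towards a larger trial, and the Discussion already names the small sample as a limitation. This stands as far as it goes. A reader might infer from the failed derivation that the trial is underpowered, or that a null result could not be interpreted. The document does not support either inference. The only SDs it gives are 2.29 and 2.67, and low power appears only under SDs that a reviewer has to assume. A confidence interval would still be informative after a null result.

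A second reply concerns timing. It is tempting to say that closure of 27 to 33% cannot belong to the primary time point, which section 2.11 places "4 weeks after the final treatment (T1, primary endpoint". But section 2.16 does not tie the literature values to that time. Section 2.12.1 also schedules weekly healing assessments during weeks 1 to 4, and the values could belong to an early week. A condensed article may leave the source time point out. This remains a query, not an error.

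Neither reply rescues the derivation. The article chose to print the formula, the inputs and the result, and to join them as cause and consequence. That is a stated calculation that fails, not a detail left to a fuller document.

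**Conclusion.** The stated formula and inputs do not produce the stated sample size. They give 4 per group by the formula and 5 by the exact t-test, or 10 to 14 in total after 20% loss. The printed total of 60 is therefore about 4.3 to 6 times what the inputs require. The definition of n as the overall size is also wrong, since the formula gives the size per group. Both conclusions rest only on figures in the document, with the two-sided test taken from section 2.20.

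The defect is an inconsistency between inputs and result, not a shortfall in power on the stated inputs. Either the means and SDs are not those used to reach 60, or 60 was reached in some other way. The document does not show which. It also gives no ground for calling 60 a feasibility size, so that reason should not be supplied on the authors' behalf. The implied effect of 2.42 SD is very large, which makes the literature SDs worth checking. That they are too small is a matter of judgement, with no contrary figure in the document.

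**What to change.** In section 2.16:

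1. Define n as the number per group.
2. Correct the inputs if they are misprinted, or print the derivation that leads to 60, or say that 60 was set on other grounds and name them. If the present inputs stay, report what they give: 4 per group by the formula and 5 by the exact t-test, or 5 and 7 after 20% loss.
3. State what 60 delivers: with 24 evaluable per arm and a two-sided 5% t-test, 90% power for a difference of 0.96 SD and 80% power for 0.83 SD.
4. As a query to the authors: confirm that 2.29 and 2.67 are SDs of percentage wound closure, and at which time point. Any table of power at larger SDs should be marked as illustrative, under assumed values.

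The cost is the rewording of one section. No extra patients are needed, and neither the design nor the analysis changes.
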